### Trial assessments

Children enrolled in the trial are followed up for up to 120 h post-enrolment or until the first primary endpoint is reached which means diarrhea resolution, whichever is earlier. The schedule of enrolment, intervention, and outcome assessments is shown in Table 2, which follows the SPIRIT (statement provides evidence-based recommendations for the minimum content of a clinical trial protocol) guidelines Table 4.

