### Discontinuation procedure

#### Criteria for removal from study and treatment failure

Patients are discharged from the hospital when diarrhea is resolved (the working definition of resolution of diarrhea has been mentioned below). However, no participants are discharged before 24 h from enrolment.If it takes more than 5 days (≥ 120 h) to resolve diarrhea or if a patient becomes dehydrated requiring unscheduled IV fluids, we transfer the patient to the general in- patient’s ward for further evaluation and treatment. In that case, it is considered a “treatment failure.”After enrollment, if any patient develops any co-morbidity like pneumonia, sepsis, electrolyte imbalance or requires specific antibiotics and/or special attention/intervention, we transfer the patients to the General ward or ICU of the hospital and are removed from the study. The reason for removal is recorded and an off-study document is completed by the study team.Patients who decide to withdraw from the study are defined as “drop-out.”Patients who do not consume at least 80% of ORS offered are considered “non-compliant”.If stool culture reveals an agent that needs antibiotic therapy, the patient is removed from the study, and an off-study document is completed by the study team.All data collected on randomized subjects are kept for intent-to-treat analysis, including patients who withdrew from the study (drop out), have co-morbidity, or are defined as treatment failures or non-compliant.

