#### Definitions

Duration of diarrhea in hospital: time in hours, from randomization till resolution of diarrhea.Resolution of diarrhea: the passage of the last liquid or semi-liquid stool before one soft/formed stool or no stool for 12 h [18].Stool output: The weight of stool in g/kg of admission body weight expressed per time period (i.e., per 24 h and for the entire duration of diarrhea).ORS and plain water intakes: The total volume (in ml) of ORS or plain water is taken per kg of admission body weight, expressed per time period.Treatment failure: If diarrhea continues for more than 120 h after enrollment, or requires unscheduled IV fluids due to progressive dehydration, requiring transfer to the general in-patient wardUn-scheduled IV: When intravenous rehydration fluids are given due to the inability of the ORS to maintain hydrationNon-compliance: inability to consume ≥ 80% of ORS

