### Statistical considerations

#### Sample size and power

The total sample size is 312 male children. In previous non-cholera studies of children comparing an anti-diarrheal to placebo [19–22], the effect sizes for the hourly duration of diarrhea and 24-h stool volume ranged from 0.3 to 1.0 (duration) and 0.3 to 0.7 (stool output), respectively. Outcome improvements ranged from 15 to 45% with treatment (vs. placebo). A clinically significant improvement of 20% produces effect sizes of 0.4 to 0.7 (duration) and 0.3 (stool output) using the pooled standard deviations reported within each outcome. When applied to conventional alpha (0.05) and beta (0.20) values, between 32 and 174 patients per group are required for statistical significance. The maximum anticipated accrual rate of 3 patients per week over 24 months results in 156 patients per group, or 132 patients per group assuming 15% attrition. Therefore, the final anticipated patient group numbers are estimated to provide >99% and 68% power to detect a 20% difference in hourly diarrhea duration and 24-h stool output, respectively.

Justification for the content of the excerpt, based on an independent samples *t*-test (in the Data Analysis part), is reviewed in Table 3. Our sample size estimates were based on detecting a difference in the primary outcome variable (duration of diarrhea). We acknowledge that we were underpowered for secondary outcomes such as stool volume. The secondary outcomes in our study were better classified as exploratory outcomes, which is why we are not adjusting our alpha for multiple endpoints.

**Table 3 Tab3:** Duration of diarrhea (days^a,b^)

Study	M_t_	SD_t_	M_p_	SD_p_	Mdiff	%diff	SDpooled	ES	20%_diff_	ES	nreq	nact	%op
Cojocaru^a^	4.05	1.48	5.73	1.77	1.68	29.3	1.62	1.0	1.14	.71	32	132	99
Santos^b^	4	2.1	4.7	2.2	0.7	14.9	2.15	0.3	0.94	0.44	81	132	99

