#### Statistical analysis

Data are collected on paper and entered electronically capturing information such as demographics, medical history, clinical assessments, clinical course, etc., and transcribed into an electronic database using Statistical Package for Social Sciences (SPSS) (version 20), STATA, or equivalent. The primary analysis will be intended to treat analysis which will include all of the patients who were randomized in the study. A per-protocol analysis will also be done only including only those randomized subjects with efficacy data on diarrhea volume and who have taken at least 80% of the investigational product. If the distribution of the variable does not have a normal distribution, a log transformation of data will be performed before the t-test analysis or a non-parametric equivalent test will be performed. Differences between the two treatment groups (VS002A versus WHO ORS) will be examined for baseline characteristics before performing a statistical analysis of the efficacy endpoints. If any differences are considered to be clinically important, subgroup analysis will be presented for the relevant endpoints. Depending upon the normality of distribution of the quantitative variables, a *t*-test or Mann-Whitney *U* test will be used to compare the duration of diarrhea, stool output, the output of vomit, and ORS intake. The chi-squared test will be used to compare treatment failures, unscheduled IV, and frequency of vomiting. Comparison of the primary outcome will be performed with and without adjustment of design effects (age stratum) and patient characteristics (cause, clinical characteristics on admission, nutritional status). All analyses will be performed separately on children as per protocol and on all children on an intention-to-treat basis. In addition, a life-table analysis will also be performed. Time to cessation of diarrhea will be compared by log-rank test, and adjustments of covariates will be made via Cox proportional hazards regression.

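### The primary test on duration of diarrhea needs a value for every child, but children transferred or unresolved at 120 h have none, and how they are scored can reverse the result

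*Protocol article*

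**What the plan says.** All places are in the protocol article.

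- **Endpoint (Definitions):** "Duration of diarrhea in hospital: time in hours, from randomization till resolution of diarrhea". No value is given for a child whose resolution is not observed.
- **End of follow-up (Trial assessments):** "Children enrolled in the trial are followed up for up to 120 h post-enrolment or until the first primary endpoint is reached", whichever comes first.
- **Earlier exits (Criteria for removal from study and treatment failure):** "or if a patient becomes dehydrated requiring unscheduled IV fluids, we transfer the patient" to the general ward, and the child counts as a treatment failure. Removal also follows co-morbidity and certain culture results: "If stool culture reveals an agent that needs antibiotic therapy, the patient is removed from the study". Data on all these children are retained for intention-to-treat.
- **Analysis (Statistical analysis):** the primary set is every randomized child. A t-test (after log transformation if needed) or a Mann-Whitney "test will be used to compare the duration of diarrhea, stool output, the output of vomit, and ORS intake". Then: "In addition, a life-table analysis will also be performed", with a log-rank test and Cox regression. Treatment failure gets its own chi-squared test and is listed as an exploratory outcome.
- **Sample size and power:** the calculation rests on an independent-samples t-test, with 156 per group, or 132 after 15% attrition.

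**The concern.** The stated test and the stated follow-up do not fit together. A t-test or Mann-Whitney on hours to resolution has nothing to use for a child who leaves observation unresolved, while intention-to-treat requires that child to be in the comparison. Someone must supply a number, drop the child, or censor, and the three choices do not give the same answer.

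The exit that matters most is transfer for unscheduled intravenous fluids. The Definitions section describes this as the ORS being unable to maintain hydration, so it is itself a sign of poor efficacy and may differ by arm. If such a child is given few hours, or disappears, the worse product gains. This is a superiority trial meant to inform WHO guidance, so a primary result that can point the wrong way is a serious matter.

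**Working it through.** **Inputs from the article.** Table 3, second planning study: control mean 4.7 days = 112.8 h; pooled SD 2.15 days = 51.6 h; 20% difference 0.94 days = 22.56 h. Group size 132 after attrition. Observation limit 120 h.

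**Assumed, because the article gives no figures.** Early-failure rates of 5% in one arm and 10% or 15% in the other; transfer uniform on 8 to 36 h (mean 22 h, variance 28²/12 = 65.3); normal durations; failure unrelated to underlying duration; two-sided 0.05.

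**1. The plan's own setting, without the limit.** Power = Φ(22.56 / (51.6 × √(2/132)) − 1.96) = 94.4% for the second study. Table 3 prints 99 in that row; the mismatch is a separate matter and does not affect this point.

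**2. The 120 h limit alone.** For X = min(T, 120) and a = (120 − μ)/σ, the mean is μ + σ[−φ(a) + a(1 − Φ(a))].
- Control: a = 0.140, mean 95.6 h, SD 32.6 h.
- 20% shorter: μ = 90.24, a = 0.577, mean 81.2 h, SD 39.5 h.
- Difference 14.4 h, standard error √((32.6² + 39.5²)/132) = 4.46 h, power Φ(14.4/4.46 − 1.96) = 90%.

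So the limit takes power from 94% to 90%. Simulated power in the same setting was similar for the t-test (90%), Mann-Whitney (91%) and log-rank (89%). With 156 per arm, log-normal durations and the SD shrinking with the mean, it was about 97% or more for the t-test and log-rank.

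**3. Early failures entered at time to transfer, no true difference.** Each failure replaces an average of 95.6 h by 22 h, a loss of 73.6 h.
- Spurious benefit: 0.05 × 73.6 = 3.7 h (10% vs 5%); 0.10 × 73.6 = 7.4 h (15% vs 5%).
- Variance in an arm with failure rate f: (1 − f)·32.6² + f·65.3 + f(1 − f)·73.6². This gives about 1268, 1448 and 1602 for f = 5%, 10% and 15%.
- Standard errors: √((1268 + 1448)/132) = 4.54 h; √((1268 + 1602)/132) = 4.66 h.
- Chance of a significant win for the worse arm: Φ(−1.96 + 3.68/4.54) = 12.5%; Φ(−1.96 + 7.36/4.66) = 35%.

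Simulation gave about 12% and 37%. Nominal is 2.5%.

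**4. Other handlings in the same setting (simulated t-test).** Excluding random failures gives about 2.5%. Excluding failures that track long duration gives 5 to 8%. Scoring failures at 120 h gives 2% or less.

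**5. Failure confined to the children with the longest underlying durations.** Simulation with 156 per arm, log-normal, control 4.7 days (SD 2.2), transfer at 6 to 36 h, no true difference. Significant wins for the arm with more failures:

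| Handling | 10% vs 5% | 15% vs 5% |
|---|---|---|
| Time to transfer, t-test | 28.4% | 77.2% |
| Time to transfer, Mann-Whitney | 23.2% | 72.0% |
| Failures excluded, t-test | 7.4% | 17.1% |
| Log-rank, censored at transfer | 9.4% | 27.6% |
| Scored at 120 h, t-test | 2.5% | 2.4% |
| Log-rank, unresolved through 120 h | 2.3% | 2.1% |

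When the worse arm was also truly 5.6 h longer (15% vs 5%), time to transfer showed it 7.4 h shorter, and the t-test favoured it in 53% of trials. With an assumed shorter control mean of 3.0 days (SD 1.5) and no true difference, the log-rank test censored at transfer favoured it in 81% (15% vs 5%).

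**The case against.** The article plans a log-rank test and Cox regression, which handle the 120 h limit properly. Treatment failures are compared separately, so an imbalance would be visible. The rule for non-resolvers is a detail that an article often leaves to the analysis plan, which is not shown. All of this is fair, but the point does not rest on a missing detail. The article states the test, the endpoint and the end of observation, and these do not fit together. The time-to-event analysis is an addition with no stated priority, and it is itself biased if transferred children are censored at transfer. A visible imbalance in failures would not correct the primary p-value.

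A reader might infer more than the text supports:

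- **That early failures are given short durations.** No section says so. Under the definition a transferred child has no duration, and keeping data for intention-to-treat does not make time to transfer the outcome. It is one possible reading.
- **That the 120 h limit is itself a major harm.** Table 3's control means and SDs would put 66% (first study) and 45% (second) of control children above 120 h under a normal distribution. But the time origin of those studies is not given, whereas this trial counts from randomization. The power loss is small, and a restricted mean to 120 h is the same capped quantity.
- **That the best of several tests will be chosen, inflating type I error.** The section selects the t-test or Mann-Whitney by distribution and nowhere plans to take the smallest p-value.
- **That the log option breaks down on zero durations.** Their frequency is unknown, and a non-parametric alternative is already offered.

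Scoring failures at 120 h is also a choice, because it counts failure against an arm. In the assumed 3.0-day case with 20% vs 5% failures, the log-rank test then favours the arm with fewer failures in 22% of trials although underlying durations are alike. For an ORS trial that is defensible, but it should be stated openly.

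**Conclusion.** The point holds in this form: the comparison listed for the primary endpoint requires a complete duration for every randomized child, and the protocol's own follow-up rules leave some children without one. Early transfer drives the risk; the 120 h limit does not.

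Its size depends on handling. Time to transfer gives about 12% or 37% wrong-direction t-test wins (10% or 15% vs 5% failures). Exclusion is harmless if failure is random, and gives 5 to 8% at 132 per arm, or 17% in the extreme case above, if it tracks long duration. Censoring at transfer gave 9% or 28% in that extreme case. Scoring at 120 h stays at or near the nominal 2.5% or below. Failure rates, transfer times and distributions are assumptions, and equal failure rates in the two arms would remove most of the directional bias. The documents show that the result is exposed to this choice; they do not show that the harmful choice will be made.

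**What to change.** Name one primary analysis: time from randomization to resolution in all randomized children, compared by log-rank test with Cox regression for adjustment, administratively censored at 120 h. Keep treatment failures in the risk set as not resolved through 120 h, and do not censor them at transfer. State in the same place how children removed for other reasons and withdrawals are handled. Report the difference in restricted mean duration to 120 h, with failures at 120 h, so that the result stays in hours. Move the t-test and Mann-Whitney, with failures ranked worst, to sensitivity analyses.

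The cost is a wording change before unblinding, since both methods are already planned. Power is similar (simulated 89% for log-rank against 90% for the t-test in the second planning setting). The small downside is that the headline becomes a hazard ratio or restricted mean and not a simple mean.

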#### Exploratory outcomes

Stool output in the 1st 24 h of hospitalization (g/kg body wt.), further divided into two 12-h periodsTotal stool output during hospitalization (g/kg body wt.)ORS intake in the 1st 24 h of hospitalization (g/kg body wt.)Total ORS intake (ml/kg body wt.)Unscheduled IV (frequency/ORS group)Treatment failure (frequency/ORS group)Output and frequency of vomitingChange in body weight (between pre-randomization and post-treatment)Urine output in the 1st 24 h of hospitalization (g/kg body wt.)Total urine output during hospitalization (g/kg body wt.)Documented infectious agentBlood chemistry (between pre-randomization and after 24 h of treatment)Gut health biomarker: citrulline (CIT) and kynurenine to tryptophan ratio (KT) between pre-randomization and at 24 hours after the enrolment)

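### Stool output and ORS intake are assigned unadjusted tests, although the trial already collects and names covariates that could sharpen these comparisons

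*Protocol article*

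**What the plan says.** All references are to the protocol article; no separate analysis plan is at hand.

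- **Adjustment.** Statistical analysis states: "Comparison of the primary outcome will be performed with and without adjustment of design effects (age stratum) and patient characteristics". The characteristics named are aetiology, clinical state at admission and nutritional status. The Cox model in the same section concerns time until diarrhea stops, which is again the primary outcome.
- **Tests for the continuous outcomes.** Depending on normality, a t-test or Mann-Whitney "test will be used to compare the duration of diarrhea, stool output, the output of vomit, and ORS intake". No covariates are mentioned.
- **Baseline imbalance.** Where a difference between arms looks clinically important, the section promises subgroup analysis of the endpoints concerned. It does not mention adjustment there.
- **Power.** Sample size and power says the group sizes are "estimated to provide >99% and 68% power to detect a 20% difference in hourly diarrhea duration and 24-h stool output, respectively", and adds: "We acknowledge that we were underpowered for secondary outcomes such as stool volume". It classes these outcomes as exploratory.
- **Outcomes with a pre-randomization value.** Exploratory outcomes lists blood chemistry before randomization and after 24 h of treatment, and "citrulline (CIT) and kynurenine to tryptophan ratio (KT) between pre-randomization and at 24 hours after the enrolment". Statistical analysis names no test for any of these.

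**The concern.** The plan accepts adjustment in principle and names the covariates, but applies them only to the outcome that needs precision least. Duration of diarrhea is said to have more than 99% power. Stool output is the only other outcome with a stated power, and it falls short of 80%. It also matters to the trial's rationale: the Background argues that mothers make limited use of standard ORS partly because it does not cut stool output.

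Subgroup analysis is a poor substitute when the arms differ at baseline. It divides the sample, widens every interval and gives no single corrected estimate of the treatment difference. A regression on prespecified covariates gives that estimate from all the children.

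At stake is the width of the intervals for 24-h stool output and ORS intake, and how chance imbalance is handled. The validity of the randomized comparison is not in question.

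**Working it through.** **Inputs.** From Sample size and power: "When applied to conventional alpha (0.05) and beta (0.20) values, between 32 and 174 patients per group are required for statistical significance"; "A clinically significant improvement of 20% produces effect sizes of 0.4 to 0.7 (duration) and 0.3 (stool output"); and accrual that "results in 156 patients per group, or 132 patients per group assuming 15% attrition". So d = 0.3, n = 132 per group (156 × 0.85 = 132.6) and alpha = 0.05. The article does not state sidedness. It also gives no R², the share of variance explained by the covariates, so R² is assumed below and shown as a range.

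**Step 1: reproduce the stated figure.** With the normal approximation, power = Φ(d·√(n/2) − 1.96). Here 0.3 × √66 = 2.437, and Φ(2.437 − 1.960) = Φ(0.477) = 0.683. The noncentral t gives 0.680. Both match the stated 68%. The required n is 2 × (1.960 + 0.842)² / 0.3² ≈ 174.4, or 175 rounded up, against 174 in the article. A one-sided test would give 78.6% and 138 per group, so the article used a two-sided, unadjusted comparison.

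**Step 2: the same children with covariates.** Adjustment multiplies the residual SD by √(1 − R²), so the effect size becomes 0.3/√(1 − R²).

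| R² (assumed) | Power, 24-h stool output |
|---|---|
| 0 (as planned) | 68% |
| 0.04 (R = 0.2) | 70.1% (normal approximation) |
| 0.05 | 70.2% (noncentral t) |
| 0.10 | 72.6% (noncentral t) |
| 0.15 | 75.0% (noncentral t) |
| 0.25 (R = 0.5) | 80.1% (noncentral t) |

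The R² needed for 80% power is 1 − n·d²/[2(1.960 + 0.842)²] = 1 − 11.88/15.70 ≈ 0.24. A gain of 5 points needs R² of about 0.11. The article describes no stool output measured before randomization, so R² would have to come from age, aetiology, admission findings and nutritional status.

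**Step 3: outcomes measured before randomization and at 24 h.** Let rho be the correlation between the two values, with equal variance at both times. Relative to the variance of the 24-h value:

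- 24-h value alone: 1
- raw change: 2(1 − rho)
- 24-h value with the baseline as covariate (ANCOVA): 1 − rho²

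ANCOVA relative to raw change is therefore (1 + rho)/2, which is 0.65, 0.75 and 0.85 at rho = 0.3, 0.5 and 0.7. Below rho = 0.5, raw change is noisier than ignoring the baseline. The article gives no rho. This step supports a choice of model; it does not measure a loss under any analysis that the article states.

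**The case against.** The strongest reply is that nothing here is wrong. An unadjusted test in a randomized trial is valid, the outcomes are declared exploratory, and the low power is admitted. The primary outcome already has adjusted and Cox analyses. The benefit is also unproven: at R = 0.2 it is about 2 points, and 80% needs covariates that explain about a quarter of the variance. All of this stands, and it limits the weight of the point. It does not remove it, because the unadjusted test for stool output and ORS intake is written into the plan while the covariates are collected in any case.

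A reader might infer something stronger: that blood chemistry, citrulline and the KT ratio will be tested as raw before-after differences. The documents do not support this. Body weight is the one outcome in that list explicitly called a change. The wording for the others may give only the sampling times, and no test is named for them. The stated aim for the gut markers is to describe concentrations and their associations with concurrent factors, and the electrolyte objective speaks of imbalance as a complication, which could be analysed as event frequencies. The choice of model may properly sit in the full protocol or the analysis plan, so it is not counted as an omission.

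**Conclusion.** The point holds as a low-cost improvement, not as an error. The plan confines adjustment to the primary outcome, assigns unadjusted tests to stool output and ORS intake, and answers imbalance with subgroups. For 24-h stool output, adjustment would move power from 68% to between about 70% and 80% over an assumed R² of 0.04 to 0.25. The range rests on the article's effect size of 0.3, 132 per group and two-sided alpha of 0.05. It would be too strong to say that the plan forgoes 80% power, because no R² is documented.

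For serum electrolytes, glucose, citrulline and the KT ratio, the conclusion is conditional: if the arms are compared, ANCOVA is the better model for any rho below 1. The primary conclusion is unaffected.

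**What to change.** In Statistical analysis:

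1. State that 24-h stool output and ORS intake, on the log scale if skewed, will also be compared by linear regression on arm plus the covariates already named for the primary outcome (age, aetiology, clinical state at admission, nutritional status). Itemise these variables before unblinding. Report the adjusted difference with its 95% CI beside the unadjusted test.
2. Let this adjusted estimate, rather than subgroup analysis, be the response to baseline imbalance in these outcomes.
3. Where serum electrolytes, glucose, citrulline or the KT ratio are compared between arms, regress the 24-h value on arm with the pre-randomization value of the same measure as covariate, rather than testing raw change.

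This needs no new data, visits or patients. It costs a few degrees of freedom, a little more analysis and the work of fixing the covariate list in advance.
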